### Individual participants

English-speaking, African Americans, 50 to 74 years of age, who are not current on CRC screening, are eligible for study participation. Individuals with a personal history of CRC or inflammatory bowel disease, blindness or severe hearing impairment; dementia; or other condition with life expectancy less than two years, are ineligible for participation.

### Sample size calculation

We intend to enroll 7,200 individuals in this study, with 1,800 enrolled in each study arm. This sample size is based on 20 NBLIC community coalitions randomized to four study arms (WA, WA + TA, IP, IP + TA). There will also be three settings (church, clinic, and community site) per coalition. Each community coalition will have 30 groups of individuals completing three consecutive EPICS sessions, recruiting 15 individuals per setting with an expected 25% dropout rate; thus, we anticipate that 12 of these individuals will complete all three sessions. For the EPICS cRCT, there will be (30 groups of three sessions) × (12 individuals completing all three sessions) × (20 NBLIC community coalitions) = 7,200 individuals. Based on data from a previously published study, we calculated intracluster correlation coefficient (ICC) to equal 0.0911 (9.1%) [6]. The effective sample size (ESS) was 5,645, which still has high power (>99%) with design effect of 1.2754.

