**Methods/design:**

In this study, investigators will recruit 20 community coalitions and 7,200 African-Americans age 50 to 74 to test passive and active approaches to disseminating the Educational Program to Increase Colorectal Cancer Screening (EPICS); to measure the extent to which EPICS is accepted and the fidelity of implementation in various settings and to estimate the potential translatability and public health impact of EPICS. This four-arm cluster randomized trial compares the following implementation strategies: passive arms, (web access to facilitator training materials and toolkits without technical assistance (TA) and (web access, but with technical assistance (TA); active arms, (in-person access to facilitator training materials and toolkits without TA and (in-person access with TA). Primary outcome measures are the reach (the proportion of representative community coalitions and individuals participating) and efficacy (post-intervention changes in CRC screening rates). Secondary outcomes include adoption (percentage of community coalitions implementing the EPICS sessions) and implementation (quality and consistency of the intervention delivery). The extent to which community coalitions continue to implement EPICS post-implementation (maintenance) will also be measured. Cost-effectiveness analysis will be conducted.

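### The sample size of 7,200 is computed as session completers but called the number enrolled, and 25% dropout from 15 does not leave 12

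*Protocol article*

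**What the plan says.** The Sample size calculation section of the protocol article opens with an enrolment target: "We intend to enroll 7,200 individuals in this study, with 1,800 enrolled in each study arm". The abstract's Methods/design paragraph agrees: "investigators will recruit 20 community coalitions and 7,200 African-Americans age 50 to 74".

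The derivation follows in the same section. The clusters are given as "This sample size is based on 20 NBLIC community coalitions randomized to four study arms", and the groups as "Each community coalition will have 30 groups of individuals completing three consecutive EPICS sessions". Each group's size comes from "recruiting 15 individuals per setting with an expected 25% dropout rate; thus, we anticipate that 12 of these individuals will complete all three sessions". The closing product is 30 groups multiplied by "12 individuals completing all three sessions) × (20 NBLIC community coalitions) = 7,200 individuals".

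Two other sections use the result. Power analysis takes 1,800 per arm as the n for all its calculations. Trial timeframe gives 7,200 as the number whose screening status will be determined at follow-up.

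**The concern.** There are two faults in one paragraph.

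- **The dropout step.** The text presents 12 as the consequence of 25% dropout from 15. It is not.
- **The label on the total.** The product counts people who attend all three sessions, yet the total is introduced as enrolment. Completion has its own meaning in this trial: the implementation protocol under Toolkit has a step for identifying those who attend all three sessions.

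What is at stake is the trial's headline number. A coalition or funder reading the article can take 7,200, 9,000 or 9,600 as the recruitment target, depending on which sentence is given priority. A reader of the power analysis cannot tell whether 1,800 per arm means people enrolled or people completing.

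**Working it through.** **Inputs, all from Sample size calculation:** 20 coalitions, 4 arms, 30 groups per coalition, 15 recruited, 25% dropout, 12 completers. Number of groups: 30 × 20 = 600.

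**Unit for the 15.** The text says per setting, with three settings per coalition. Read literally, 15 × 3 × 20 = 900 recruited, which cannot lead to 7,200. The product works only if 15 and 12 refer to a session group, so that reading is used below.

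**The plan's own figure.** 30 × 12 × 20 = 7,200, and 7,200 / 4 = 1,800 per arm. Both reproduce exactly, but only as completers.

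**The dropout step.**
- 15 × (1 − 0.25) = 11.25, not 12.
- 1 − 12/15 = 0.20, so going from 15 to 12 is a 20% dropout.
- 12 / (1 − 0.25) = 16, so 12 completers at 25% dropout need 16 recruited.
- 12 × 1.25 = 15. Inflating by 1.25 instead of dividing by 0.75 would produce the printed pair, as would rounding 11.25 up. The article does not say which happened.

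**Carried through 600 groups.**

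| Assumption | Enrolled (per arm) | Completing (per arm) |
|---|---|---|
| 15 per group, 25% dropout (as stated) | 9,000 (2,250) | 6,750 (1,687.5) |
| 15 per group, 20% dropout | 9,000 (2,250) | 7,200 (1,800) |
| 16 per group, 25% dropout | 9,600 (2,400) | 7,200 (1,800) |
| 7,200 taken as enrolled, 25% dropout | 7,200 (1,800) | 5,400 (1,350) |

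Shortfall on the stated inputs: 7,200 − 6,750 = 450, and 450 / 7,200 = 6.25%.

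**Effect on the stated power for hypothesis three.** The article's design effect of 1.2754 is taken as printed; whether it is right is a separate question. The effective n per arm is then:
- 1,800 / 1.2754 = 1,411
- 1,687.5 / 1.2754 = 1,323
- 1,350 / 1.2754 = 1,058

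For the changes used in Power analysis (34.8% against 15.5%, and 22.9% against 13.1%; two-sided alpha 0.05), power stays above 99% at all three sizes.

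**The case against.** The best defence is that 11.25 was rounded to 12 around a rate described only as expected, that the product openly labels its factor as completers, and that nothing in the stated hypothesis three power depends on the difference. The last part stands. It also stands if clustering is taken at the coalition (5 per arm, ICC 0.0911), in the sense that the choice of count hardly moves the effective n per arm: 1,800 / (1 + 359 × 0.0911) = 53.4; 1,687.5 / (1 + 336.5 × 0.0911) = 53.3; 1,350 / (1 + 269 × 0.0911) = 52.9. Rounding may explain the 12, but it adds 0.75 of a person in each of 600 groups, and it does not explain why a completer total is called enrolment.

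A reader might infer more than the article supports:

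- **That the analysed number falls to 5,400, or 25% below plan.** The 25% concerns attendance at all three sessions. Primary outcome measures specifies intention-to-treat, and Trial timeframe plans to determine screening status for 7,200. Missing a session is not loss to follow-up, so 7,200 enrolled and 7,200 analysed could both hold. What cannot hold is 7,200 enrolled and 7,200 completing.
- **That recruitment will stop at 7,200.** No such rule is stated. Operationally, recruitment is set at 15 for each group.
- **That Reach or hypothesis one changes.** Reach has its own formula, people receiving three sessions over eligible people in the target settings, and neither term is the 7,200 target. Hypothesis one compares enrolment between dissemination approaches. No definition or figure for either is shown to change.
- **That the enrolled number should be named the intention-to-treat denominator.** Primary outcome measures models adherence among all African Americans aged 50 to 74 in the targeted communities, and its effectiveness formula divides by those reached. Naming the enrolled number would add a further inconsistency.

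**Conclusion.** The error is certain on the article's own figures. A 25% dropout from 15 does not give 12, and 7,200 is a completer count presented as enrolment. As stated, the inputs give 9,000 enrolled and 6,750 completing, 450 (6.25%) fewer than 7,200. If 7,200 really is the enrolled number, 5,400 would complete; that is a completer count and not necessarily the analysed number.

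The figures rest on two assumptions: that 15 applies to a session group, and that dropout means not attending all three sessions. The consequence is for the clarity of the recruitment target and of the n in the power analysis. The stated power for hypothesis three is not materially affected under the article's own design effect. The correction should be made because the wrong figure is the trial's headline sample size and is cheap to put right.

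**What to change.** State the enrolled and completing numbers separately, say that 15 is per session group, and reconcile the dropout rate in one of these ways:

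1. Keep 25%: 9,000 enrolled (2,250 per arm), 6,750 expected to complete (about 1,688 per arm).
2. Correct the dropout to 20%, if that is the real assumption: 9,000 enrolled, 7,200 expected to complete (1,800 per arm).
3. Keep both 25% and 7,200 completers: 16 per group, 9,600 enrolled.

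Carry the chosen figures into the abstract, Sample size calculation, Power analysis and Trial timeframe, and say whether 1,800 per arm in the power analysis counts people enrolled or people completing. Under option 1, if the effective sample size is meant for completers, it also changes: 6,750 / 1.2754 = 5,292 in place of 5,645, with the printed design effect.

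Options 1 and 2 correct stated figures only and leave the design as it is. Option 3 adds 600 people to recruitment (9,600 − 9,000) and is therefore a change to the trial, not just to the text.

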**Figure 1 F1:**
[figure not shown]
CONSORT flow diagram for EPICS cRCT.

Randomization at the organizational (community coalition) level has been chosen because this will minimize contamination that may occur if individual participants are randomized. In utilizing cluster randomization, we will focus on community coalitions as the cluster for all study arms, with individuals within their target settings as the secondary unit. We will ensure balance in all four study arms by ordering them into groups based on the total number participating. A computer program generating random numbers between 1 and *n* will be used to assign community coalitions to one of four conditions: web access (WA) to facilitator training materials and toolkits without technical assistance (TA); the same as 1, but with technical assistance (TA); in-person access (IP) to facilitator training materials and toolkits without TA; and in-person access to facilitator training materials and toolkits with TA. Our multilevel approach (*e.g.*, cluster, setting, and individual) promotes widespread dissemination [13]. Community coalitions will be allocated to one of the four arms and informed consent will be obtained from community coalition members and from individual participants.

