### Power analysis

Power calculations were performed to further justify our proposed sample size. All of these assume a sample size of 1,800 per study arm, a significance level of 5% (*i.e.* alpha = 0.05), and a two-sided two-group chi-square test of proportions. Calculations were performed using nQuery Advisor, version 7. These are performed for hypothesis one (H1) and hypothesis three (H3); hypothesis two (H2) is qualitative, so power calculations do not apply. For H1, we anticipate that there will be 25%, 33%, and 50% greater participant enrollment with the Web + TA arm, IP arm, and IP + TA arm, respectively, when compared to the passive web-based-only arm (based on our prior experience with community coalition based studies). Comparisons of any of these proportions to any proportion that is obtained for the passive web-based arm (for example, 5%, 10%, or 20%) will result in greater than 99% power to detect differences in the proportions as being statistically significant. For H3, we can obtain estimates of cancer knowledge change over time (pre-intervention to post-intervention percentages with the correct response) for a small group education cohort and a control cohort from Blumenthal, Smith *et al.*[6]. These estimates include changes of 34.8 (71-36) and 15.5 (55.2-39) for a CRC perceived risk question, and 22.9 (92.9–70) and 13.1 (88.5–75.for a CRC screening question. Assuming that we observe similar changes in our study participants for active and passive arms, we will have greater than 99% power to detect differences in the proportions as being statistically significant.

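### The design effect of 1.2754 drops the 1 from the formula and uses 15-person session groups instead of randomised coalitions of 360; at the plan's own ICC the effective sample is about 214, not 5,645

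*Protocol article*

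**What the plan says.** The Trial design section (text below Figure 1) randomises coalitions: "we will focus on community coalitions as the cluster for all study arms". The Sample size calculation section builds the total from the same units. "This sample size is based on 20 NBLIC community coalitions randomized to four study arms", and "Each community coalition will have 30 groups of individuals completing three consecutive EPICS sessions", with 15 people recruited and 12 expected to complete in each group. Thus 30 × 12 × 20 = 7,200. An ICC of 0.0911 is taken from the earlier trial of the intervention. The section then concludes: "The effective sample size (ESS) was 5,645, which still has high power (>99%) with design effect of 1.2754".

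The Power analysis section gives the contrasts for hypotheses 1 and 3 and again reports more than 99% power. Its basis is: "All of these assume a sample size of 1,800 per study arm", with a two-sided, two-group chi-square test of proportions at 5%.

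**The concern.** A design effect near 1.28 is implausibly small for 20 clusters of several hundred people with an ICC of 0.09. Either the formula or the cluster size had to be wrong, and both turn out to be.

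The sentence is the plan's only argument that 7,200 people in 20 coalitions are enough once clustering is allowed for. With five coalitions per arm, precision depends mainly on the number of coalitions and hardly at all on the number of people in each. If the claim stands, a null comparison of dissemination strategies would be read against a stated power above 99% and could be taken as evidence that the strategies are equivalent.

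**Working it through.** **Inputs.** From Sample size calculation: N = 7,200; 20 coalitions in four arms (5 per arm, or 10 v 10 for active v passive); 30 groups per coalition; 15 recruited and 12 completing per group; ICC = 0.0911. From Power analysis: two-sided alpha 0.05 and the contrasts for hypotheses 1 and 3.

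**1. Reproduce the plan's figures.**
- (15 − 1) × 0.0911 = 1.2754, exact to four decimals.
- 7,200 / 1.2754 = 5,645.3.

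Both printed figures are recovered, but only with the leading 1 left out. The standard formula gives 1.2754 only at m = 1 + 0.2754 / 0.0911 = 4.02, a cluster size that appears nowhere in the article.

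**2. Restore the 1, keep the session group.** 1 + 14 × 0.0911 = 2.2754, and 7,200 / 2.2754 = 3,164.

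**3. Use the randomised cluster.** m = 30 × 12 = 360 (equally 7,200 / 20).
- Design effect = 1 + 359 × 0.0911 = 33.70.
- Effective sample size = 7,200 / 33.70 = 213.6, or about 53 per arm and 107 per side for active v passive.
- Ratio to the stated figure: 5,645 / 213.6 = 26.
- With 20 coalitions at this ICC, the effective sample cannot exceed 20 / 0.0911 = 220, however many people are enrolled.
- A design effect of 1.2754 with 360 per coalition would need an ICC of 0.2754 / 359 = 0.00077, about 1/119 of the stated value.

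**4. Power at coalition level.** With k coalitions per side, SE² = [p1(1 − p1) + p2(1 − p2)] × DE / (360k). Power is from the noncentral t with 2k − 2 degrees of freedom (18 or 8).

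Example: hypothesis 3, screening question, 22.9 v 13.1 points treated as proportions, as the plan does. The bracket is 0.1766 + 0.1138 = 0.2904.
- 10 v 10: SE = √(0.2904 × 33.70 / 3,600) = 0.0521; 0.098 / 0.0521 = 1.88; power 43%.
- 5 v 5: SE = √(0.2904 × 33.70 / 1,800) = 0.0737; 0.098 / 0.0737 = 1.33; power 22%.

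The perceived-risk question (34.8 v 15.5) gives 88% and 54%.

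**5. Sensitivity to the ICC.** Rows below 0.0911 are assumptions. Detectable differences are for 80% power from a base of about 34% to 37%. That base is also an assumption, taken from the earlier results of 33.9% and 37.3% in the Background.

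| ICC | Design effect | Effective N | Detectable, 10 v 10 | Detectable, 5 v 5 | Screening-question power, 10 v 10 | 5 v 5 |
|---|---|---|---|---|---|---|
| 0.01 | 4.59 | 1,569 | 7 points | 11 points | 99.8% | 88% |
| 0.02 | 8.18 | 880 | 10 | 15 | 95% | 66% |
| 0.05 | 18.95 | 380 | 15 | 23 | 66% | 35% |
| 0.0911 | 33.70 | 214 | 20 | 30 | 43% | 22% |

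**6. Hypothesis 1.** The article does not say whether 25%, 33% and 50% greater enrolment is relative or absolute.
- Absolute points over 5%, 10% or 20%, 5 v 5 coalitions, ICC 0.0911: +25 points gives 88%, 81% and 71%; +50 points stays above 99%.
- Relative increases, same setting: about 6% to 19%.
- Relative reading with 1,800 independent people per arm and no clustering: 37% (5% v 6.25%), 66% (10% v 12.5%) and 95% (20% v 25%). On this reading the claim already fails before clustering is considered.

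**The case against.** The strongest point is that 214 depends on 0.0911 being an ICC between coalitions. The article does not say at what level it was estimated. The source trial is described as 369 people in one metropolitan area, randomised to interventions, so the value may reflect small groups rather than coalitions. This stands: 214 must be given as the result at the plan's own ICC, with a range beside it. It does not rescue 5,645, because every coalition ICC from 0.01 upward gives 1,569 or less.

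Second, not every contrast loses its power. The +50-point version of hypothesis 1 keeps more than 99% even at ICC 0.0911. Restoring only the 1 at m = 15 leaves the hypothesis 3 contrasts at about 99.9% or more. This also stands. The claim fails as a general statement, not for each contrast, and the loss of power comes mainly from the wrong cluster level.

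Third, 360 counts completers, whereas the Reach denominator is all eligible people in the target settings, a larger number that is not given. That is correct, but the effective sample then only moves from 214 towards the ceiling of 220.

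Fourth, the article gives no power for CRC screening, which may simply be condensation. No weight is placed on it here. The GEE analysis with robust inference concerns the analysis and does not change the sizing.

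**Conclusion.** The sample size statement is wrong as written, on two counts that follow from the article's own numbers. The 1 is missing from the design effect, and the cluster used is the recruited session group rather than the randomised coalition. At ICC 0.0911 the design effect is 33.7 and the effective sample about 214, against 1.2754 and 5,645. The size of the shortfall depends on the coalition-level ICC; over an assumed 0.01 to 0.05 the effective sample is 1,569 to 380.

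More than 99% power is not supported as a general claim. Even at an assumed ICC of 0.01, the screening-question contrast has 88% power arm v arm. At ICC 0.0911 the trial could detect differences in screening of about 20 points (active v passive) or 30 points (arm v arm). The second is well above the 16.2-point gap (33.9% − 17.7%) between small-group education and control in the earlier trial, and here every arm delivers the intervention. The detectable differences rest on the assumed 34% to 37% base and on equal coalition sizes.

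**What to change.** Rewrite the end of the Sample size calculation section:

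- State the design effect as 1 + (360 − 1) × ICC for outcomes measured in completers. For Reach, use the expected number of eligible people per coalition.
- Report an effective sample of about 214 at ICC 0.0911, with rows for coalition ICCs of 0.01 to 0.05, and say at what level 0.0911 was estimated.
- Withdraw the claim of more than 99% power here and in the Power analysis section, where 1,800 per arm must be reduced for clustering.
- Say whether the hypothesis 1 increases are relative or absolute.
- Give detectable differences for Reach and for CRC screening, using t critical values on cluster degrees of freedom (18 for 10 v 10, 8 for 5 v 5).
- Name active v passive as the contrast with usable precision. Presenting pairwise arm comparisons as estimates with intervals is a recommendation; the correction does not depend on it.

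This is a rewording and needs no extra participants. The cost is a much less favourable power statement. If the sponsor wants more precision, it has to come from more coalitions rather than more people per coalition. The article says 33 coalitions exist and 20 are to be used. At ICC 0.0911 all 33 would raise the ceiling on the effective sample only from 220 to 33 / 0.0911 = 362.

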### Hypotheses

We propose three hypotheses to measure the impact of our effort:

Hypothesis one (H1): When compared to passive dissemination, active dissemination will result in greater participant enrollment.

Hypothesis two (H2): The intervention will be offered with equal fidelity in churches, clinics, and community sites.

Hypothesis three (H3): Knowledge of CRC screening and perceived risk of CRC will be positively correlated.

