2. Implementation Protocol: We also developed and tested a protocol similar to that used in the original CCSIT study and converted it into non-academic language. This 12-step protocol includes procedures to: recruit community partners; schedule sessions; market the program; recruit participants; prepare for the sessions; sort the toolkit; assign facilitators; deliver the sessions; identify ‘completers’ (participants attending all three intervention sessions); monitor screening; submit reports; and get technical assistance.

3. EPICS Curriculum: Individual participants in all study arms will complete three small group educational sessions. These sessions, each approximately one-hour in length, will be conducted the same day/time of the week for three consecutive weeks. This schedule will be formulated by NBLIC community coalitions in conversation with intervention settings at a time likely to solicit the greatest participation.

4. Individual/participant CRC educational materials include three session-specific brochures, CDC consumer education materials, including: Get Smart in Your Family Dinner; Get Smart as You Shop; and CRC Facts on Screening.

5. Individual/participant incentives such as a cookbook, water bottles, shopping bag, and similar items are distributed to individuals completing all three EPICS sessions.

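### The >99% power given for H3, a correlation, is for an active-versus-passive difference in proportions, with gaps borrowed from an education-versus-control comparison

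*Protocol article*

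**What the plan says.** Under Hypotheses, the protocol article states H3 as "Knowledge of CRC screening and perceived risk of CRC will be positively correlated". No arm or dissemination strategy appears in it.

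The Power analysis section covers H1 and H3 and treats H2 as qualitative. One set of assumptions serves every calculation: "All of these assume a sample size of 1,800 per study arm", a two-sided 5% level and a "two-sided two-group chi-square test of proportions". For H3 the inputs are pre-to-post changes in the percentage answering correctly, taken from the earlier trial "for a small group education cohort and a control cohort". They are 34.8 and 15.5 points for a perceived-risk question, and 22.9 and 13.1 points for a screening question. The conclusion is: "Assuming that we observe similar changes in our study participants for active and passive arms, we will have greater than 99% power". What is powered there is a between-arm gap in proportions.

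Under Toolkit, the curriculum item says: "Individual participants in all study arms will complete three small group educational sessions". The Trial design and Toolkit sections show that the arms differ in how facilitators are trained and supplied, and in whether technical assistance is given. They do not differ in whether participants are taught.

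**The concern.** There are two separate faults.

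**Hypothesis and calculation do not match.** H3 asks whether people who know more about screening also perceive more risk. The calculation asks whether the share with a changed answer differs between arms, one item at a time. Both items could differ by arm with no correlation within participants. They could also be strongly correlated with no arm difference. A result on one question does not settle the other.

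**The effect size comes from another kind of comparison.** The borrowed gaps are 34.8 − 15.5 = 19.3 points and 22.9 − 13.1 = 9.8 points, education against control. Assigning the control cohort's change to the passive arms gives people who complete all three sessions the change seen in a cohort that, by the article's Background, had no significant gain in knowledge.

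At stake is the credibility of one of the only two hypotheses used to support the sample size. A reader would take H3 as settled on power when no power for it has been given.

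**Working it through.** **Inputs.** From Power analysis: 1,800 per arm, two-sided 5%, changes of 34.8 v 15.5 and 22.9 v 13.1 points. From Sample size calculation: 7,200 people, 20 coalitions, ICC 0.0911, design effect 1.2754, effective sample size 5,645. Derived: 20/4 = 5 coalitions per arm and 7,200/20 = 360 people per coalition. The gaps in step 2 and the correlations in step 3 are my assumptions, because the article gives none.

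**1. Reproducing the stated figure.** Treat the changes as proportions p1 and p2, with mean p̄ and gap d:

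power = Φ{[d√n − 1.96√(2p̄(1−p̄))] / √(p1(1−p1) + p2(1−p2))}

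- Perceived risk, 0.348 v 0.155, n = 1,800: (8.188 − 1.203)/0.598 = 11.7, power >99.9%.
- Screening, 0.229 v 0.131, n = 1,800: (4.158 − 1.065)/0.539 = 5.7, power >99.9%.
- With n = 1,800/1.2754 = 1,411, both stay >99.9%.

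The arithmetic is right for the contrast calculated. Treating pre and post as separate proportions and testing a difference in differences also leaves >99.9% and 99.98%, so that simplification does not matter to the stated result.

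**2. Smaller gaps between arms that are all taught.** Same formula, base 34.8%, 1,800 per arm, no clustering:

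| Assumed gap (points) | Power |
|---|---|
| 19.3 (borrowed) | >99.9% |
| 10 | >99.9% |
| 5 | 89% |
| 3 | 48% |
| 2 | 24% |

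Worked line for 5 points: (0.05 × √1,800 − 1.296)/0.660 = (2.121 − 1.296)/0.660 = 1.25, and Φ(1.25) = 0.89.

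**3. H3 as written.** Power for a correlation r by Fisher's z: Φ{atanh(r)√(n−3) − 1.96}.

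| n | r for 99% power | r = 0.05 | r = 0.10 | r = 0.20 |
|---|---|---|---|---|
| 7,200 independent | 0.051 | 98.9% | >99.9% | >99.9% |
| 5,645 (stated effective size) | 0.057 | 96% | >99.9% | >99.9% |
| 214 (stress case) | 0.287 | 11% | 31% | 84% |

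The stress case assumes that ICC 0.0911 applies at coalition level: design effect 1 + 359 × 0.0911 = 33.7, and 7,200/33.7 = 214. Applying that design effect to a correlation is itself a rough assumption.

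**4. The borrowed gaps with clustering.** Noncentral t on coalitions, noncentrality d/√[(p1(1−p1) + p2(1−p2))/n_eff]:

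| Assumption | Perceived risk | Screening |
|---|---|---|
| ICC 0.0911 at coalition level, 5 v 5 (n_eff 53.4 per arm; 8 df) | 54% | 22% |
| ICC 0.0911 at coalition level, 10 v 10 (n_eff 106.8 per side; 18 df) | 88% | 43% |
| ICC 0.01 (assumed) at coalition level, 10 v 10 | >99% | >99% |
| ICC 0.0911 in groups of 12 (design effect 2.0), 5 v 5 | >99% | >99% |

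The first two rows are a stress case. The article does not say at which level, or for which outcome, its ICC was estimated.

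**The case against.** The strongest defence is that active against passive is the trial's central contrast, and that H3 may simply be loosely worded. Developers train the facilitators in the active arms, while passive coalitions train themselves. The Cost-effectiveness analysis section expects active strategies to be delivered with more fidelity. A gap in knowledge change is therefore plausible. This stands. A reader might infer that identical sessions imply a zero gap, and hence a rejection rate of only 5%. The article does not support that: zero is the null value, and the design expects delivery to differ. What the article lacks is support for gaps of 19.3 and 9.8 points.

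A second tempting inference is that clustering destroys the power. The Sample size calculation section does report a design effect, and with it the borrowed gaps keep >99%. The low figures in step 4 need the ICC to hold at coalition level, which the article does not say.

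A third is that the passive arms are treated as untaught or untreated. The article calls the comparator only a control cohort and does not say what it received.

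Finally, H3 is not among the listed primary or secondary outcomes, and 7,200 is built up as 30 × 12 × 20, not from H3. That limits the consequences. It does not make the stated power apply to H3.

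**Conclusion.** The point holds as a mismatch of hypothesis, test and source of effect. The figure above 99% is arithmetically correct for the contrast calculated, but it is not power for H3 as worded. If H3 was meant as an arm comparison, the assumed gap is unsupported, and power depends heavily on what replaces it: from >99.9% at 10 points to 24% at 2, for 1,800 independent people per arm and a 34.8% base.

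It would be wrong to conclude that H3 as a correlation is underpowered. With 7,200 independent people, or with the stated effective size, r of about 0.05 to 0.057 suffices for 99% power. Only under the coalition-level ICC assumption does power for small correlations fall away (about 31% at r = 0.10). The correction should be made, but it does not touch enrolment, allocation or the primary outcomes.

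**What to change.** Remove the present >99% as the power for H3 and choose one of two routes.

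(a) Keep the correlation. Test it with a participant-level model of perceived risk on knowledge, clustered on coalition. State the detectable r with the ICC, its level and the resulting design effect; step 3 gives a starting range.

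(b) Restate H3 as an active-versus-passive difference in change in knowledge and perceived risk. Justify a gap suited to arms that all receive the sessions, and allow for clustering by coalition.

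Either route costs some rewording and one recalculation, with no change to the design or data collection. Under (a) the restated power may still be high. Under (b) it is likely to be lower if the justified gap is smaller than the borrowed one.
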